#### Descriptive Statistics

Continuous variables will be presented as either mean (SD) or median with IQR, depending on their distribution as assessed by visual inspection of histograms and normal quantile plots. Categorical variables will be described using frequencies and percentages. For comparisons between groups (pregnancies with and without placental insufficiency–related complications), independent-samples 2-tailed *t* tests or Mann-Whitney *U* tests will be used for continuous variables, and the chi-square test or Fisher exact test will be used for categorical variables, as appropriate.

#### Primary Objectives: Prediction Model Development

Multivariable logistic regression will serve as the primary analytical approach for prediction model development at 3 gestational windows (11‐13 weeks, 26‐28 weeks, and 35‐36 weeks of gestation) to address both primary objectives 1 and 2. Clinically relevant candidate predictors are predefined and entered into multivariable models, followed by model reduction to achieve parsimony (eg, backward elimination with a retention threshold of *P*<.10). Nonlinear relationships between continuous variables and the log odds of the outcomes will be tested with the inclusion of polynomial terms up to the third degree, which will be kept in the model if statistically significant.

For each patient, this method estimates a predicted probability of developing the outcome based on the log odds of the outcome. For primary objective 1, the predicted probabilities can be used to define low- and high-risk subgroups at predefined gestational age thresholds. Specifically, a risk threshold will be defined based on clinically relevant screen-positive rates (eg, 10%, 15%, or 20%) to balance sensitivity and specificity for clinical implementation. For primary objective 2, logistic regression will similarly provide predicted probabilities. In addition, Fine and Gray competing risks time-to-event models will be used as sensitivity analyses accounting for delivery without the outcome of interest (preeclampsia or FGR) as a competing event.

To further improve upon current FMF prediction models, a Bayesian updating approach will be applied to refine existing FMF first-trimester risk estimates using additional biomarkers and clinical variables collected later in pregnancy. The FMF first-trimester risk estimate will be used as the prior probability. Likelihood ratios derived from biomarker and biophysical measurements at 26 to 28 weeks and 35 to 36 weeks will be incorporated via Markov chain Monte Carlo simulations to generate updated posterior risk distributions. This enables dynamic, individualized risk reassessment as pregnancy progresses.

All models will undergo internal validation using 5-fold cross-validation with repeated iterations to obtain stable performance estimates. Model performance will be evaluated using the following metrics:

Model discrimination: AUC-ROC and c-statisticCalibration assessment: calibration plots and calibration slope and intercept on cross-validated dataClinical utility: sensitivity, specificity, positive and negative predictive values, and screen-positive ratesComparison against existing risk assessment methods: NICE and ACOG guidelines for preeclampsia risk scoring

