This prospective cohort study aims to develop enhanced prediction models for placental dysfunction–related complications and define optimal delivery timing. Candidate predictors will be selected a priori based on four guiding principles: (1) established inclusion in validated prediction models and current screening approaches (maternal characteristics, MAP, uterine artery Doppler, and angiogenic biomarkers used in the FMF prediction models), (2) biological plausibility and prior evidence linking placental dysfunction and maternal cardiovascular maladaptation with preeclampsia and FGR (eg, ophthalmic artery Doppler and arterial stiffness measures), (3) feasibility of implementation within routine maternity care pathways, and (4) the potential incremental predictive value of novel biomarkers derived from stored biospecimens and exploratory omics approaches. By integrating clinical factors, biophysical parameters, and maternal circulating biomarkers across 3 critical gestational windows, this study will improve risk stratification and guide clinical decision-making in perinatal care. Furthermore, the comprehensive dataset and biobank will facilitate investigation of novel biomarkers and pathophysiological mechanisms underlying placental dysfunction.

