#### Sample Size Estimation

We estimate a 10% to 15% participation rate from the approximately 5000 annual deliveries at GCUH. On the basis of a prevalence of 10% for placental dysfunction–related disorders (preeclampsia and SGA or FGR), approximately 200 cases with these outcomes are expected. In the development of prediction models using binary outcomes (high-risk or low-risk) with a 10% incidence rate and up to 15 predictors, targeting an area under the receiver operating characteristic curve (AUC-ROC) of 0.75, the estimated sample size is approximately 1700 participants [42].

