x PIV: pulsatility index for veins.

y RI: resistive index.

z EDV: end-diastolic velocity.

aa PSV: peak systolic velocity.

ab HbA_1c_: hemoglobin A_1c_.

ac OGTT: oral glucose tolerance test.

ad PPROM: preterm premature rupture of membranes.

ae FBS: fetal blood sampling.

af SCN: special care nursery.

ag NICU: neonatal intensive care unit.

ah GH: gestational hypertension.

ai GDM: gestational diabetes mellitus.

A subset of samples has undergone preliminary biomarker quantification, including measurement of angiogenic markers (sFlt-1 and PlGF), and additional omics-based analyses are underway. Interim analyses have been conducted comparing clinical variables and biomarkers between participants with and without complications. It is anticipated that 2 to 3 primary publications will be ready in late 2026 or early 2027, including evaluation of maternal circulating biomarkers and exploratory analyses of novel biomarker candidates identified through omics techniques.

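### Significance-tested quadratic and cubic terms are not counted in the 15-predictor budget, and with no shrinkage step the fitted risks will be too extreme

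*Protocol article*

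**What the plan says.** Sample Size Estimation assumes a model "with a 10% incidence rate and up to 15 predictors, targeting an area under the receiver operating characteristic curve (AUC-ROC) of 0.75" and concludes that "the estimated sample size is approximately 1700 participants". It names no shrinkage or optimism criterion, only a reference.

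Primary Objectives: Prediction Model Development makes logistic regression the primary approach in all three gestational windows. Predefined candidates are entered, "followed by model reduction to achieve parsimony (eg, backward elimination with a retention threshold of" P<.10). Nonlinearity in continuous variables is tested with "polynomial terms up to the third degree, which will be kept in the model if statistically significant". The elimination method is offered as an example; the polynomial rule is not.

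On validation, "All models will undergo internal validation using 5-fold cross-validation with repeated iterations". The list of performance metrics that follows includes calibration slope and intercept on cross-validated data. The section describes no penalisation, shrinkage or recalibration of the final coefficients.

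Results reports that recruitment closed at 1267 enrolled: 1072 completed pregnancies, 144 ongoing, and 51 withdrawn or with missing or duplicated data.

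**The concern.** What drives overfitting is the number of parameters searched, not the number of named predictors. A continuous predictor tested up to the third degree brings three candidate parameters, of which the budget counts one. Terms kept because they reached significance in a limited sample have, on average, exaggerated coefficients. Without shrinkage the published equation then pushes high risks too high and low risks too low.

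The individual risk equation is the product of both primary objectives, and its predicted probabilities set the high-risk and low-risk groups. Miscalibration would carry straight into those groups. If the same selection also sits outside the cross-validation, the reported AUC would overstate what a new cohort will show.

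**Working it through.** **Inputs.** From Sample Size Estimation: 10% incidence, AUC 0.75, 15 predictors, about 1700 participants. From Results: 1072 + 144 = 1,216 usable at most. Assumed: shrinkage target S = 0.90.

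**Step 1: reproduce 1700.** Under a binormal linear predictor, AUC 0.75 at 10% incidence corresponds to a Cox-Snell R² of 0.0748. The shrinkage criterion is

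n = p / [(S − 1) × ln(1 − R²/S)].

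With S = 0.90, ln(1 − 0.0748/0.90) = −0.0868, so n = 15 / (0.10 × 0.0868), about 1,729. This is within 3% of 1700. The companion criteria (optimism in R², precision of overall risk) give 597 and 139, so shrinkage drives the size.

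**Step 2: count the polynomial candidates.** Each continuous predictor adds two.

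| Continuous predictors among 15 | Candidate parameters | n at S = 0.90 | Events per parameter at n = 1,216, 10% incidence |
|---|---|---|---|
| 0 | 15 | 1,729 | 8.1 |
| 5 | 25 | 2,881 | 4.9 |
| 8 | 31 | 3,572 | 3.9 |
| 10 | 35 | 4,033 | 3.5 |
| 15 (ceiling) | 45 | 5,185 | 2.7 |

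The absolute numbers depend on S: with p = 15 the formula gives 1,085 at S = 0.85 and 3,657 at S = 0.95. The inflation does not, because n is proportional to p at any fixed S: 25/15 = 1.67 times and 35/15 = 2.33 times.

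**Step 3: shrinkage expected at the available size.** Solving the same formula for S:

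| n | 15 parameters | 30 | 45 |
|---|---|---|---|
| 1700 | 0.90 | 0.82 | 0.75 |
| 1,216 | 0.86 | 0.76 | 0.68 |

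At 10% incidence 1,216 participants give about 122 events, where the article says "approximately 200 cases with these outcomes are expected". Each window-specific dataset and each component outcome can only have the same or fewer.

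**Step 4: simulate the strategy.** All runs use n = 1,216, 15 candidate predictors and backward elimination at P<.10, with no shrinkage. Predictor distributions, effects and the significance level for polynomials are assumptions, since the article gives none of them.

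| Setting | Calibration slope in new data | AUC in new data | AUC, final model only cross-validated |
|---|---|---|---|
| 15 continuous, 5 true linear effects, polynomials at P<.10, 122 events | 0.72 | 0.731 | 0.761 |
| 15 continuous, 8 true linear effects, polynomials at P<.05, 10% incidence | 0.82 | 0.731 | 0.742 |
| 8 continuous and 7 binary, about 112 events | 0.78 | – | – |
| 6 continuous, polynomials at P<.05, about 10% incidence | 0.88 | 0.750 | 0.757 |
| As second row, assumed 3% incidence | 0.54 | 0.688 | 0.734 |

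The mixed setting gave a slope of about 0.5 with about 33 events. In the 10% incidence rows that report AUC, the overstatement is 0.761 − 0.731 = 0.030, 0.742 − 0.731 = 0.011 and 0.757 − 0.750 = 0.007. At 3% it is 0.734 − 0.688 = 0.046.

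With every selection step repeated in each fold, the first two settings gave cross-validated AUCs of 0.727 and 0.709 against 0.731 in new data. The AUC optimism is gone, at the price of some pessimism.

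Without the polynomial search, the slope was 0.90 rather than 0.82 in the second setting and 0.81 rather than 0.78 in the mixed one. The polynomial rule therefore costs calibration, but some shrinkage is needed even without it.

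**The case against.** - **Backward elimination is only an example and does little harm alone.** This largely stands. With linear terms only, slopes at n = 1,216 were 0.81 to 0.92, and cross-validating the final model overstated AUC by less than 0.01. The weight of the point falls on the polynomial rule, which is stated firmly, and on the missing shrinkage.
- **Forty-five parameters and about 5,185 participants are an extreme.** This stands. A reader might take them as the plan's true requirement, but that needs all 15 predictors to be continuous, and Table 1 lists many categorical items such as smoking, diabetes and chronic hypertension. Yet the markers the article stresses (mean arterial pressure, uterine artery pulsatility index, PlGF, sFlt-1, augmentation index, ophthalmic artery indices) are continuous, so 5 to 10 is a fair working range.
- **Reported AUC need not be optimistic.** This stands as a condition. A reader might infer that cross-validation applies only after reduction; the text does not say so, and a condensed article may leave fold-level detail to the full plan. The too-extreme coefficients do not depend on that reading.
- **Overfitting would be seen.** True in part: calibration slope is planned and external validation is a later phase. Seeing a slope below 1 does not correct the equation.
- **The interim comparisons.** A reader might link "Interim analyses have been conducted comparing clinical variables and biomarkers between participants with and without complications" with "Candidate predictors will be selected a priori based on four guiding principles" and infer that outcome data are shaping the candidate list. Nothing in the article says so; the modelling section calls the candidates predefined, and Descriptive Statistics plans such group comparisons anyway.

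**Conclusion.** The concern holds in this form: the sample size counts 15 parameters, while the modelling rule searches more, probably 25 to 35. On the basis that reproduces 1700, that search needs about 2,880 to 4,030 participants, against at most 1,216 usable. Followed as written and without shrinkage, the equations will give risks that are too extreme, with a calibration slope of about 0.7 to 0.9 at 10% incidence and about 0.5 at an assumed 3%. Optimism in the cross-validated AUC, about 0.01 to 0.03 at 10% incidence and more with fewer events, follows only if elimination and polynomial selection are left outside the folds.

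The shrinkage target of 0.90 is an assumption that reproduces the stated figure; the article does not give it as its criterion. The slopes and AUCs depend on simulated predictors with truly linear effects, which is unfavourable to a polynomial search. Their direction is secure; their exact size is not.

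**What to change.** 1. Count nonlinear terms within the 15-parameter budget. Restrict them to a few continuous predictors named in advance, and drop retention by significance.
2. Shrink the final coefficients. Penalised logistic regression is the more direct route. The alternative is to multiply the coefficients by the cross-validated calibration slope, taken from folds that repeat all selection steps, and re-estimate the intercept. That slope can over-shrink: in the second simulated setting it was 0.68 against 0.82 in new data.
3. State that every data-driven step (elimination, polynomial choice, penalty tuning, choice of risk threshold) is repeated inside each fold.
4. Restate the sample size passage for the parameters actually searched and the sample obtained, and name the criterion used.

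The cost is a few sentences of plan text and standard R code. The equations become slightly less simple, and the reported performance will be lower.

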**Methods:**

The Placental Health Study is a prospective cohort study conducted at the Maternal Fetal Medicine Unit at Gold Coast University Hospital, Australia. Singleton pregnancies are enrolled at 11 to 13 weeks, 26 to 28 weeks, and 35 to 36 weeks of gestation and are followed until delivery. Exclusion criteria are multiple pregnancies, major fetal anomalies, maternal age below 18 years, and inability to provide informed consent. Clinical data, standardized ultrasound and Doppler measurements, hemodynamic parameters, and biospecimens (serum, plasma, whole blood RNA, and urine) are collected at each visit. Three gestational age-specific datasets (11‐13 weeks, 26‐28 weeks, and 35‐36 weeks) will be constructed for model development. Prediction models will be developed using multivariable logistic regression. Competing risks (Fine and Gray) models will be used as sensitivity analyses for outcomes related to gestational age at delivery. Bayesian updating will be applied to refine existing Fetal Medicine Foundation risk estimates using additional biomarkers or variables collected later in pregnancy. Developed models will undergo internal validation via 5-fold cross-validation, with performance assessed through model discrimination, calibration, and comparison against existing approaches. Collected biospecimens will also be analyzed for angiogenic markers and exploratory omics studies.

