### Study Objectives

#### Primary Objectives

The primary objectives of this study are as follows:

To improve current predictive models or develop new predictive models for placental dysfunction–related pregnancy complications, including preterm preeclampsia and FGR, at 2 critical gestational periods: the first trimester (11‐13 weeks) and the second trimester (26‐28 weeks)To establish third-trimester (35‐36 weeks) models to predict term preeclampsia and FGR and to define the optimal time for delivery.

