## Results

Recruitment for the Placental Health Study commenced in June 2022. By the close of recruitment in February 2026, a total of 1267 participants were enrolled. Of these, 1072 (84.6%) participants had a completed pregnancy, 144 (11.4%) participants are still to complete their pregnancy, and 51 (4%) had withdrawn or with missing or duplicated data. Comprehensive clinical data, including maternal demographics, medical and obstetric history, ultrasound measurements, Doppler indices, hemodynamic parameters, pathology laboratory results, and pregnancy outcomes, were collected through integration with electronic medical records (Table 1). Data were recorded in REDCap. Maternal serum, plasma, whole blood for RNA extraction, and urine samples have been collected and processed according to standardized operating procedures. Biospecimens are stored at −80 °C.

**Table 1. T1:** Summary of data and sample collection throughout pregnancy.

Assessment period and category	Data collected
At enrollment	
Demographic data	Date of birth, age, height, weight, BMI, ethnicity, smoking, and alcohol use status
Medical history	Diabetes mellitus, chronic hypertension, systemic lupus erythematosus, and antiphospholipid syndrome
Obstetric history	Miscarriage, termination, parity, previous preterm birth, preeclampsia, FGR^a^, placental abruption, and placenta previa
Risk assessment	Preeclampsia risk scoring (NICE^b^ and ACOG^c^ guidelines)
11‐13 weeks assessment	
First-trimester risk assessment	NIPT^d^ results (risk of trisomies, fetal sex, risk of monosomy X, sex chromosome aneuploidy risk, 22q11.2 deletion risk, and fetal fraction [cfDNA^e^, %], FGR risk, and preterm preeclampsia risk
Ultrasound and Doppler	Fetal biometry (CRL^f^ and NT^g^), fetal Doppler (ductus venosus A-wave), maternal Doppler (right and left uterine artery PI^h^ and mean PI), biophysical markers (cervical length and measurement method), and ultrasound markers (nasal bone, tricuspid regurgitation, cardiac activity, FHR^i^, holoprosencephaly, diaphragmatic hernia, atrioventricular septal defect, exomphalos, and megacystis)
BP^j^	Systolic BP, diastolic BP, and MAP^k^
Biochemical markers	Free beta-hCG^l^, PAPP-A^m^, PlGF^n^, sFlt-1^o^, and sFlt-1:PlGF ratio
Clinical pathology	Urine test, full blood count, chemistry panel, and recent iron infusion date (if available)
26‐28 and 35‐36 weeks	

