These advancements in preterm preeclampsia screening have prompted updates to national [50,51] and international [52] guidelines, recommending implementation of the prediction model with prophylactic low-dose aspirin to reduce preterm preeclampsia incidence and associated adverse outcomes. A cost-effectiveness analysis in Australia demonstrated significant benefits of this screening strategy, including prevention of 31 preterm preeclampsia cases and cost savings of approximately Aus $1.43 million (Aus $1=US $0.72 as of August 27, 2020) over a 2-year period [53]. Despite these clinical benefits, the FMF first-trimester prediction model has not yet become a standard component of routine maternity care for all health care providers in Australia. Gold Coast University Hospital has implemented FMF-based first-trimester preeclampsia screening in routine clinical care, providing a valuable setting to generate evidence supporting broader application in clinical practice.

Current prediction models still have limited accuracy for predicting term preeclampsia and SGA due to their complex etiology. Although considered less severe, term complications constitute most cases, occurring at least twice as frequently as preterm preeclampsia, and impose a significant health care burden [26]. While the first-trimester screening combined with low-dose aspirin effectively prevents preterm preeclampsia, it showed limited efficacy for term preeclampsia [24]. A prediction model at 35 to 36  weeks’ gestation, using maternal factors and biomarkers, can identify approximately 70% of pregnancies at risk of developing term preeclampsia [54]. In addition, planned birth at term is a potential prevention strategy for term preeclampsia [55,56]. A recent secondary analysis from a prospective nonintervention cohort study has demonstrated that a risk-stratified approach based on a combined prediction model at 35 to 36  weeks’ gestation with timed birth is likely able to reduce the risk of term preeclampsia [27]. However, research on individualized risk assessment models at late gestation to determine optimal delivery timing remains limited. This cohort study will facilitate the development of refined prediction models and optimal delivery timing strategies to reduce term preeclampsia incidence and improve pregnancy outcomes.

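### At 11–13 weeks no stated analysis compares the new model with the recorded FMF risk or estimates what other first-trimester markers add to it

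*Protocol article*

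**What the plan says.** All references are to the protocol article.

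- **Primary Objectives.** Objective 1 is "To improve current predictive models or develop new predictive models" for complications including preterm preeclampsia and FGR, in the first trimester (11–13 weeks) and at 26–28 weeks.
- **Prediction Model Development, method.** "Multivariable logistic regression will serve as the primary analytical approach for prediction model development at 3 gestational windows". Candidates are predefined and the model is then reduced; backward elimination at P<.10 is given as an example.
- **Same section, use of FMF.** A separate paragraph, introduced as a way to improve further on the FMF models, says that "a Bayesian updating approach will be applied to refine existing FMF first-trimester risk estimates using additional biomarkers and clinical variables collected later in pregnancy". It continues: "The FMF first-trimester risk estimate will be used as the prior probability". And: "Likelihood ratios derived from biomarker and biophysical measurements at 26 to 28 weeks and 35 to 36 weeks will be incorporated".
- **Same section, performance metrics.** The comparison item names NICE and ACOG preeclampsia risk scoring. The Abstract (Methods) promises only "comparison against existing approaches".
- **Table 1, 11–13 weeks.** The recorded items include "FGR risk, and preterm preeclampsia risk", and also PAPP-A, free beta-hCG, sFlt-1, fetal fraction, cervical length and the ductus venosus A-wave.
- **Discussion.** "Gold Coast University Hospital has implemented FMF-based first-trimester preeclampsia screening in routine clinical care". The same section ranks FMF above risk-factor checklists.

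**The concern.** The only step that builds on FMF brings in data from the two later windows, and FMF is not on the itemised list of comparators. Followed as written, the 11–13-week work yields a newly fitted logistic model judged against NICE and ACOG. The article already says that FMF does better than checklists of that kind. Beating them would therefore not show a gain over the screening that women at this hospital already receive.

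Two questions would stay open at 11–13 weeks: whether the new model is better than the recorded FMF risk, and whether first-trimester markers outside the FMF combination add anything to it. The data for preterm preeclampsia appear to be in hand, so the gap lies in the stated analyses and not in the data collection.

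**Working it through.** **1. What each stated analysis does at 11–13 weeks**

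| Stated analysis | Uses FMF risk? | Informs a gain over FMF at 11–13 weeks? |
|---|---|---|
| Multivariable logistic regression, all three windows | Not stated | Not unless FMF is also evaluated on the same women |
| Bayesian updating | Yes, as prior | No; likelihood ratios come from 26–28 and 35–36 weeks |
| Comparison with existing methods | Not listed | No; NICE and ACOG only |

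**2. The plan's own figure.** The sample size (10% incidence, up to 15 predictors, AUC 0.75, about 1700 women) can be reproduced with the standard minimum-sample-size criteria for a binary prediction model. A normal linear predictor with AUC 0.75 at 10% prevalence gives a Cox–Snell R² of 0.0748. With target shrinkage S = 0.90 (assumed; not stated):

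n = P / [(S − 1) ln(1 − R²/S)] = 15 / [(−0.10) × ln(1 − 0.0748/0.90)] ≈ 1729.

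The other two criteria give 597 and 139, so 1729 governs, within 3% of 1700. The figure is sound for fitting a new 15-predictor model; it contains no calculation for a gain over FMF. With the 1267 enrolled, expected shrinkage is about 0.87 on the same inputs.

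**3. Events available.** Completed plus ongoing pregnancies: 1072 + 144 = 1216. This is an upper bound for the 11–13-week window, because women may join at any stage before 37 weeks and the number per window is not reported. The article gives no preterm preeclampsia rate for the cohort. Assumed rates of 1%, 2% and 3.3% give about 12, 24 and 40 events.

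**4. What could happen if FMF is ignored.** The Introduction's 75% detection of preterm preeclampsia at a 10% screen-positive rate corresponds, under a binormal model, to AUC = Φ[(0.674 + 1.282)/√2] = 0.917. Cohorts of 1216 were simulated with 10 FMF components, 5 new markers and backward elimination at P<.10. Sets A, B and C differ in assumed effect sizes. Correlation means that between the FMF score and the true local score. All of these inputs except P<.10 and the 0.917 are assumptions.

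| Setting | New model AUC | FMF-based AUC |
|---|---|---|
| A: 2%, correlation 1 | 0.88 | 0.91 alone; 0.91 updated |
| B: 2%, correlation 1 | 0.899 | 0.920 alone; 0.919 updated |
| C: 2%, correlation 1, equal weights | 0.880 | 0.906 alone; 0.905 updated |
| C: 2%, correlation 1, three dominant components | 0.898 | 0.910 |
| C: 2%, correlation 0.95, three dominant components | 0.900 | 0.895 |
| C: 10%, AUC 0.75, correlation 1 | 0.739 | 0.754 |
| C: 10%, AUC 0.75, correlation 0.95 | 0.742 | 0.742 |
| C: 10%, AUC 0.75, correlation 0.90 | 0.739 | 0.731 |

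At 2% and correlation 1, detection at 10% screen-positive was 62% (new) against 70% (FMF alone) in set A, and 66% against 72% in set B. The new model's calibration slope was 0.76 and 0.78; the updated model's was 0.97 and 0.94.

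In set B at correlation 0.95, updating won in 69% of runs at 2% prevalence but in 29% at 3.3%. At 0.90 the new model usually won. With FMF AUC 0.80 and correlation 0.95, updating won in 97–98% of runs (sets A and B).

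**5. Reading.** The ordering turns on local FMF fit. Where results are given for both, the updated model did not raise AUC above FMF alone. The case for fitting it is that it tests added value and avoids loss, not that it promises a higher AUC.

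**The case against.** The strongest reply is that the plan is less closed than it looks.

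- Objective 1 joins its two branches with "or". A new first-trimester model meets it. A reader might infer that half the objective goes unanswered, but the wording does not support that. What remains is the separately stated aim of improving on FMF.
- A reader might also infer that the plan relearns everything from scratch and never combines FMF information with other markers. The documents do not show this. The Introduction draws candidates both from FMF components and from novel biomarkers, and multiples of the median come from published equations. The candidate list is not printed, and nothing bars FMF risk as a covariate; that detail may sit in a fuller plan.
- The Abstract's general wording on existing approaches could include FMF, and its sentence on Bayesian updating is looser than the Methods text.
- The simulations rest on invented effect sizes, and the advantage of FMF shrinks or reverses when its local fit is imperfect. The Discussion's statement that FMF performs consistently summarises other studies and not this cohort.
- Table 1 does not say which algorithm produced the FGR risk, and the article's FMF detection figures for growth are for SGA, not Delphi-defined FGR.

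All of this stands as a limit on the point. It does not remove it. The Methods text itself fixes the updating windows and itemises the comparators, and on both counts FMF at 11–13 weeks is absent. This is an objection to what is stated, not to detail left for an analysis plan.

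**Conclusion.** The point holds in a limited form. As written, no stated 11–13-week analysis compares the new model with the recorded FMF risk or estimates what first-trimester markers outside FMF add to it. The study could therefore report a first-trimester model without showing that it is better than the FMF screening already routine at the site.

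The size cannot be fixed from the documents. If FMF fits the local population well and preterm preeclampsia is near 2%, a newly fitted model might lose about 0.02–0.03 in AUC and 6–8 percentage points of detection against FMF (sets A and B for detection). If the correlation with local truth is about 0.90, the new model tends to be the better one. A reader might conclude that updating FMF is the superior method; the simulations do not support saying so in advance.

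For preterm preeclampsia, the identification of the recorded risk with FMF rests on the Discussion's account of routine screening and on the plan's own use of FMF risk as prior. For FGR it is unconfirmed.

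**What to change.** Keep the planned logistic model. In women with a recorded first-trimester FMF risk:

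1. Add FMF risk to the itemised comparators at 11–13 weeks, evaluated on the same women. Report the cross-validated difference in AUC, detection at a fixed screen-positive rate, and calibration.
2. Beside the planned model, report one pre-specified update model per outcome: the outcome regressed on logit(recorded FMF risk), with intercept and slope re-estimated, plus a short list of first-trimester markers not in FMF. Give a likelihood-ratio test of the added terms.
3. Apply this to preterm preeclampsia. Apply it to FGR only if the recorded FGR risk is confirmed to come from the FMF algorithm.
4. Report both models and make no advance claim about which will perform better.

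**Cost.** Plan wording, one extra model and one extra comparison per outcome, using risks already recorded; no new data collection.

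**Downside.** The analysis is limited to women with a recorded first-trimester risk, and the estimates will be imprecise. With 24 events and true detection of 75%, the 95% half-width for one detection rate is 1.96 × √(0.75 × 0.25/24) ≈ 0.17; with 12 events it is about 0.25 and with 40 about 0.13. The added-value result should be reported with its interval, and a non-significant test should not be read as no gain.
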